## Abstract

**Background:**

Neuropathic pain after spinal cord injury (SCI), both traumatic and non-traumatic, is refractory to various treatments. Spinal cord stimulation (SCS) is one of the neuromodulation therapies for neuropathic pain, although SCS has insufficient efficacy for neuropathic pain after SCI. The reasons are presumed to be inappropriate locations of SCS leads and conventional tonic stimulation itself does not have a sufficient analgesic effect for the pain. In patients with past spinal surgical histories, the cylinder-type leads are likely to be placed on the caudal side of the SCI because of surgical adhesions. Differential target multiplexed (DTM) stimulation is one of the latest new stimulation patterns that is superior to conventional stimulation.

**Methods:**

A single-center, open-label, randomized, two-way crossover trial is planned to investigate the efficacy of SCS using DTM stimulation placing a paddle lead at the appropriate site for neuropathic pain after SCI in patients with spinal surgical histories. The paddle-type lead delivers energy more efficiently than a cylinder-type lead. This study consists of two steps: SCS trial (first step) and SCS system implantation (second step). The primary outcome is rates of achieving pain improvement with more than 33% reduction 3 months after SCS system implantation. The secondary outcomes are to be evaluated as follows: (1) effectiveness of DTM and tonic stimulations during the SCS trial; (2) changes of assessment items from 1 to 24 months; (3) relationships between the result of the SCS trial and the effects 3 months after SCS system implantation; (4) preoperative factors associated with a long-term effect, defined as continuing for more than 12 months; and (5) whether gait function improves from 1 to 24 months.

**Discussion:**

A paddle-type lead placed on the rostral side of SCI and using DTM stimulation may provide significant pain relief for patients with intractable neuropathic pain after SCI in patients with past spinal surgical histories.

**Trial registration:**

Japan Registry of Clinical Trials (jRCT) jRCT 1042220093. Registered on 21 November 2022, and last modified on 6 January 2023. jRCT is approved as a member of the Primary Registry Network of WHO ICTRP.

## Background

Spinal cord injury (SCI) induces paralysis and other dysfunctions, typically pain symptoms, in 30–80% of SCI patients [1–4]. Pain symptoms after SCI consist mainly of musculoskeletal and/or neuropathic pain [5, 6]. The pain after SCI impairs quality of life, and lost productivity and the cost of treatment pose a heavy economic burden for patients and their families, as well as society [2–4]. The damaged spinothalamic tracts after SCI are related to enhanced neuronal excitability and reduced descending pain inhibition, leading to chronic central neuropathic pain [7–9]. On a cellular level, microglial cells and astrocytes are activated in the early phase after SCI to remove debris and damaged cells [10]. These glial cells can be persistently activated and release several chemicals, which contribute to the development of central sensitization and neuropathic pain. In addition, hypersensitive neurons in the dorsal column of the spinal cord mediate pain secondary to increased aberrant background activity and altered sodium channel currents. Non-traumatic causes, such as spinal tumors, vascular malformations, or chronic spinal compression, may also induce spinal cord parenchymal damage. Such spinal damage can also induce neuropathic pain through a similar pathogenic mechanism as traumatic SCI. Various treatments have been used for the neuropathic pain after SCI, including medication, rehabilitation, psychotherapy, and neuromodulation therapy, but these treatment methods do not provide sufficient pain relief [11–14].

Spinal cord stimulation (SCS) is one of the neuromodulation therapies, and it has been used for decades to treat chronic neuropathic pain [15, 16]. The conventional paresthesia-based SCS uses tonic stimulation that induces a sense of paresthesia [17, 18]. It is essential that the elicited paresthesia overlaps the painful area to ameliorate pain symptoms [19]. Conventional SCS for neuropathic pain after SCI has success rates of approximately 30% [13, 14, 20]. The success rates are lower than of SCS for failed back surgery pain syndromes or peripheral neuropathic pain. Therefore, the efficacy of SCS for neuropathic pain after SCI is controversial, and current treatment guidelines do not recommend it [20–23]. The reasons are assumed to be due mainly to two factors: SCS leads may be not placed at an appropriate location, and conventional tonic stimulation itself may have an insufficient analgesic effect for neuropathic pain after SCI.

In patients with past spinal surgical histories, the cylinder-type leads are likely to be placed on the caudal side of the SCI because of adhesions around previous surgeries. The pain relief mechanism of SCS is based on the gate control theory [24, 25]. According to that theory, an appropriate SCS lead location is not on the caudal side, but on the rostral side of the SCI, which induces activation of spinal GABAergic interneurons in the dorsal horn and descending pain-inhibitory pathways [24, 25]. The first clinical question is whether SCS with a paddle-type lead placed on the rostral side of the SCI provides more pain relief. A paddle-type lead device can deliver energy more efficiently than a cylinder-type lead device, although laminectomy is necessary for paddle-type lead placement [26–28].

Recently, several new stimulation patterns without paresthesia have been developed [29–32]. Differential target multiplexed (DTM) stimulation (Medtronic Inc., Minneapolis, MN, USA) is one of the latest paresthesia-free SCS patterns, and it has the potential to be superior to conventional tonic stimulation [33]. DTM stimulation uses multiple electrical signals, and it has been shown to modulate gene expressions in the spinal cord at the site of stimulation [34–36]. Modulation of glial cells and neurons and rebalancing their interactions are considered to be among the mechanisms of pain relief by DTM stimulation [34–36]. Activity and modulation of glial cells are key factors in both neuropathic pain after SCI and DTM stimulation [10, 34–36]. The second clinical question is whether SCS using DTM stimulation provides more pain relief than conventional tonic stimulation for neuropathic pain after SCI.

We hypothesized that DTM stimulation using a paddle-type lead placed on the rostral side of the SCI provides sufficient pain relief for patients with intractable neuropathic pain after SCI with past spinal surgical histories. In fact, we have reported three cases of good outcomes using this method [26]. The aim of this study is to evaluate this hypothesis.

## Methods/design

### Study design

This is a prospective, single-center, open-label, randomized, two-way crossover, exploratory trial.

### Patient population

Patients are selected based on the inclusion and exclusion criteria described below. The main criterion for enrollment is intractable neuropathic pain after traumatic or non-traumatic SCI with histories of spinal surgery at the site where the SCS lead will pass or be placed. Patients will be recruited from new patient from standard clinical practice at Nagoya University Hospital.

### Inclusion criteria

▪ Patients with intractable neuropathic pain after SCI resistance to drug treatments▪ Patients with histories of spinal surgery at the site where the SCS lead will pass or be placed▪ 18 years of age or older▪ Visual analog scale (VAS) score for pain greater than 40 points▪ Patients classified as Frankel grade B–E▪ Patients in whom a paddle-shaped lead can be placed on the rostral side of the spinal cord lesion▪ Patients who have given written, informed consent.

### Exclusion criteria

▪ Patients for whom local and general anesthesia cannot be performed▪ Patients classified as Frankel grade A▪ Patients receiving anti-cancer therapy▪ Patients with a history of drug abuse▪ Patients at high risk for surgery, such as patients with unstable angina pectoris and with end-stage liver disease presenting with hepatic encephalopathy▪ Patients with diabetes mellitus who are not well controlled (HbA1c ≥9%)▪ Patients with serious complications (liver disease, kidney disease, heart disease, lung disease, blood disease, brain disease, etc.)▪ Pregnant or potentially pregnant patients▪ Patients considered inappropriate by a head of research or investigator

### Who will take informed consent?

Potential participants will be identified from patients who visit Nagoya University Hospital. After assessment by clinical research physicians regarding inclusion and exclusion criteria, the study information will be given to potential participants. Written and verbal informed consent will be obtained. The right of a participant to refuse to participate in this trial without giving reasons for the decision will be respected. This trial does not involve collecting biological specimens for storage.

### Study procedures

This trial consists of a two-step procedure. The first step is an SCS trial, and the second step is SCS system implantation. The lead locations for the SCS trial and SCS system implantation are the sides caudal and rostral to the SCI, respectively. In the SCS trial, two cylinder-type leads (Model 977A190; Medtronic Inc., Minneapolis, MN, USA) are to be inserted on the caudal side of the SCI under local anesthesia, so that the lead does not pass through the SCI. Once inserted, the two leads are directly sutured to the skin at the puncture sites without skin incision. The order of stimulation patterns of DTM or tonic is randomly assigned to two courses evenly (Fig. 1). One course is DTM stimulation (Stim-1), then tonic stimulation (Stim-2), and the other course is in reverse order. Each stimulation pattern is performed for two days. The stimulation off period is set as one day between Stim-1 and Stim-2 to washout previous stimulation effects (Stim-off).

**Fig. 1 Fig1:**
[figure not shown]
The order of stimulation patterns. The order of stimulation patterns of DTM or tonic is randomly assigned to two courses. One course is DTM stimulation (Stim-1), then tonic stimulation (Stim-2). The other course is in reverse order. Each stimulation pattern is performed for two days. The stimulation off period is set as one day between Stim-1 and Stim-2 (Stim-off)

After the SCS trial, the inserted leads are removed whether or not analgesic effects are obtained. In cases of an effective SCS trial or the patient agrees to implantation of an SCS system even after a non-effective SCS trial, the second step follows. With an interval of 1 month from the SCS trial, a paddle-type lead is placed on the rostral side of the SCI by laminectomy under general anesthesia (Fig. 2). The location of the lead is confirmed by intraoperative X-ray and motor-evoked potential monitoring. At the same time, an implantable pulse generator (IPG) (Intellis; Medtronic Inc.) is implanted on the hip, and it is connected to the paddle-type lead. After the SCS implantation, an effective stimulation pattern that showed efficacy in the SCS trial is started, and the analgesic effects are evaluated. In the absence of analgesic effects in the previous SCS trial, DTM stimulation is tried.

**Fig. 2 Fig2:**
[figure not shown]
Intraoperative photograph of a paddle-type lead placing. **A** The spinal dura matter is exposed by laminectomy under general anesthesia. **B** A paddle-type lead is inserted at the epidural space

### Setting stimulation parameters

Tonic stimulation delivers mild electrical pulses and elicits paresthesia. Stimulation parameters include frequency, pulse width, and voltage. Frequency (10–100 Hz) and pulse width (40–300 µs) are set by clinical research physicians so that the patient feels comfortable with paresthesia. The voltage is adjusted by the patient using a remote controller to the intensity level of eliciting comfortable paresthesia for 2 days.

DTM stimulation delivers multiple electrical signals and stimulates multiple locations without paresthesia. DTM stimulation consists of one stimulation signal on the upper side of the lead, called the base program, and multiple stimulation signals on the lower side of the lead, called the prime program. For the base program, frequency (50 Hz), pulse width (200 µs), and voltage (approximately 70% of the paresthesia threshold) are set. For the prime program, frequency (300 Hz), pulse width (170 µs), and voltage (approximately 65% of the paresthesia threshold) are set. DTM stimulation delivers electrical signals from one base and three prime programs. DTM stimulation is set by clinical research physicians; the stimulation continues for 2 days, and the patient does not adjust the stimulation parameters.

### Criteria for discontinuing or modifying allocated interventions

Any patients requesting to end their participation in the study can be withdrawn from the study regardless of the stage they have reached in the study process. Patients do not have to provide the reason of withdrawal. Patients found to be pregnant or those judged ineligible to continue participating in the study by the investigators will also be withdrawn from the study.

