### Clinical assessments

At entry, clinical research physicians obtain information from patients regarding age, sex, past history, medications, cause of SCI (traumatic or non-traumatic), level of SCI (cervical, thoracic, lumbar), location of pain (arm, leg, lower back, back, chest), degree of paralysis (none, mild, moderate, severe), sensory disturbance (hypoesthesia, allodynia, numbness), duration of disease, and Frankel grade (B-E). During the SCS trial, the degree of pain is evaluated using a VAS according to the plan (Table 1). After SCS system implantation, assessment items are evaluated according to the plan, including degree of improvement of pain relief, mental health, comprehensive health, and gait function (Table 1). Six months after SCS system implantation, if no improvement of any of the assessment items is seen, removal of the implanted SCS system would be considered.

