### Secondary outcomes

The secondary outcomes are as follows: (1) evaluation of effectiveness of DTM and tonic stimulations in the SCS trial; (2) evaluation of changes of assessment scores, VAS, SF-MPQ-2, PCS, QIDS-J, and SF-36^®^, at 1, 3, 6, 12, 18, and 24 months from SCS system implantation; (3) relationship between the result of the SCS trial and the effect 3 months after SCS system implantation; (4) evaluation of preoperative factors associated with a long-term effect, defined as continuing for more than 12 months; (5) evaluation whether there is improvement of motor function using the gait function scale (FAC) at 1, 3, 6, 12, 18, and 24 months from SCS system implantation; and (6) adverse events related to this study 3 months after SCS system implantation.

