### Statistical analysis

The primary outcome will be estimated as the probability of patients achieving more than 33% pain improvement on the VAS at 3 months after SCS system implantation. The secondary outcome analyses are as follows:A logistic regression analysis using stimulation timing (Stim-1, Stim-2), stimulation pattern (tonic, DTM), pre-VAS values for each stimulation, and interaction between stimulation timing and stimulation pattern as explanatory variables. The carryover effect is examined by testing the interaction term at a significance level of 10%. If a carryover effect is observed, an additional analysis will be performed using only Stim-1.Adjusted means and 95% confidence intervals (CIs) of the rate of change or amount of change for each item (VAS, SF-MPQ-2, PCS, QIDS-J, and SF-36^®^) are calculated for each evaluation time point including pre-implantation and post 1, 3, 6, 12, 18, and 24 months using linear mixed models with time points as fixed effects. The amount of change of each item at each time point is compared after using the Dunnet-Hsu correction for multiple comparisons.For the patients undergoing implantation, logistic regression will be performed to investigate the relationship between the efficacy of the SCS trial (DTM) and the effectiveness for 33% improvement on the VAS at 3 months after implantation.Preoperative factors associated with long-term effects are examined using logistic regression analysis as explanatory variables for the following items: sex, age (<60 years vs. ≥60 years), disease duration, pain site (arm, leg, lower back, back, chest), level of SCI (cervical, thoracic, lumbar), paralysis (none, mild, moderate, severe), sensory disturbance (hypoesthesia, allodynia, numbness), and Frankel classification (B, C, D, E).Probability of gait improvement is estimated, defining an improvement as 1 point or more in the FAC category. The probability of improved cases and the 95% CIs will be calculated at each evaluation time point.

Safety analysis will be performed by tabulating the number and probability of each event.

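### Pregnancy-led and investigator-led stops are fixed as study withdrawal, with no stated route to remain in follow-up after implantation

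*Protocol article*

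**What the plan says.** All references are to the protocol article.

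- The section headed "Criteria for discontinuing or modifying allocated interventions" covers two kinds of departure. The first is at the patient's request and is open at any point in the trial: "Any patients requesting to end their participation in the study can be withdrawn from the study regardless of the stage they have reached in the" [...]. The second is not the patient's choice: "Patients found to be pregnant or those judged ineligible to continue participating in the study by the investigators will also be withdrawn from the study". The article gives no criteria for the investigators' judgement.
- Study procedures, in the paragraph after Figure 1, describes the second step. A paddle lead is placed by laminectomy and "an implantable pulse generator (IPG) (Intellis; Medtronic Inc.) is implanted on the hip, and it is connected to the paddle-type lead".
- Clinical assessments treats lack of effect separately. At six months, "if no improvement of any of the assessment items is seen, removal of the implanted SCS system would be considered". That sentence does not mention leaving the study.
- Secondary outcomes plans assessments at 1, 3, 6, 12, 18 and 24 months. Its safety item is "adverse events related to this study 3 months after SCS system implantation".
- Statistical analysis gives the safety method: "Safety analysis will be performed by tabulating the number and probability of each event". The section on non-adherence and missing data says that nothing statistical will be done to make up for missing values.
- The retention section books interviews and stimulator adjustments for all patients. The harms section has data on all serious adverse events entered in the database. Neither mentions patients who have been withdrawn.

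**The concern.** Ending a study treatment and ending observation are different events, and for an implant the difference matters more than usual. Leaving the study does not end exposure to the lead and generator. Asking about adverse events and completing questionnaires can continue whether or not the study intervention does, provided the patient consents.

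The section does not draw this distinction. The word *also* puts pregnancy-led and investigator-led stops on the same footing as a patient who asks to leave, and *will* makes the consequence mandatory. The ordinary meaning of study withdrawal is that study observation ends.

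Two things are at stake. One is precision, because every patient lost is a large share of a very small trial. The other is selection. The trial is open-label, and the investigators who judge continued eligibility know how each patient is doing. If their judgement is related to outcome or to harm, the results describe those who were kept in.

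**Working it through.** **1. The rule against the other sections.** The claim concerns wording, so the first check is to set the sections side by side.

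| Section | What it settles | Does it keep a withdrawn patient under observation? |
|---|---|---|
| Criteria for discontinuing or modifying | Study withdrawal is the only action; mandatory for pregnancy and investigator judgement | No |
| Clinical assessments | Removal of the system is considered at 6 months for lack of improvement; not called withdrawal | Does not address it |
| Secondary outcomes | Adverse events at 3 months; other outcomes to 24 months | Does not address it |
| Provisions for post-trial care | Who covers harm | No; concerns cover, not data |
| Participant retention | Visits booked for all patients | Does not address withdrawn patients |
| Adverse event reporting and harms | Serious events entered in the database, no time limit given | Does not address withdrawn patients |
| Missing data | No statistical compensation | No |

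No section gives the status *off the study intervention but still followed* to a patient stopped for pregnancy or by the investigators.

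**2. The plan's own figure.** The sample size of 10 rests on feasibility. At 2 to 4 eligible patients a year, 10/4 = 2.5 years and 10/2 = 5 years, which agrees with the stated 3 to 5 years. No dropout or event rate is given, so what follows is illustration.

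**3. Loss of precision for safety.** Assume that all 10 patients are implanted and that w = 0 to 3 are withdrawn before 3 months and not followed, leaving n = 10 − w. With no events seen, the one-sided 95% upper bound is 1 − 0.05^(1/n). The chance of seeing at least one event at an assumed true rate of 10% is 1 − 0.9^n.

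| w | n | Upper bound, 0 events | Chance of ≥1 event at 10% |
|---|---|---|---|
| 0 | 10 | 25.9% | 65.1% |
| 1 | 9 | 28.3% | 61.3% |
| 2 | 8 | 31.2% | 57.0% |
| 3 | 7 | 34.8% | 52.2% |

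Implantation is conditional (Study procedures), so fewer than 10 may be implanted. Each withdrawal is then more than 1/10 of the implanted patients.

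**4. Selective loss, safety.** If x events are recorded and w patients are unobserved, the true count lies between x and x + w. With x = 0 and w = 2, the record shows 0/8 (Clopper-Pearson 95% CI 0 to 36.9%), while the truth may be anything from 0/10 to 2/10 (20%, 95% CI 2.5 to 55.6%). The upper end is a constructed worst case.

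**5. Selective loss, efficacy.** Assume 5 responders among 10, that those withdrawn before 3 months are all non-responders, and that they drop out of the denominator. The estimate then moves as follows (Clopper-Pearson 95% CI):

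- w = 0: 5/10 = 50.0% (18.7 to 81.3%)
- w = 1: 5/9 = 55.6% (21.2 to 86.3%)
- w = 2: 5/8 = 62.5% (24.5 to 91.5%)
- w = 3: 5/7 = 71.4% (29.0 to 96.3%)

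**The case against.** The strongest reply is that this is a journal article condensed from a fuller protocol, and that data collection after withdrawal is the kind of detail an article leaves out. That would answer a complaint about silence. It does not answer the rule that is printed: the article states a mandatory consequence and gives no alternative to it. The reply does limit what may be concluded, and several stronger readings should be set aside.

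- *Stopping the intervention always means leaving the study.* A reader might infer this from the section heading. The text does not support it. The sentence concerns continued participation, not patients whose stimulation merely stops, and Clinical assessments contemplates removal for lack of effect without calling it withdrawal.
- *Safety follow-up is declared to end with the device still in place.* No section says either thing. The first follows only from the ordinary meaning of study withdrawal, and the second is a possibility.
- *Complications of later removal go unrecorded because of this rule.* The adverse-event outcome is set at 3 months and removal for lack of improvement is considered at 6. Events after such a removal fall outside that outcome for every patient, withdrawn or not.
- *Patients doing badly are the likeliest to leave.* This is plausible in an open-label trial, but nothing in the article shows it.

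It is also fair to say that the pregnancy route is narrow, since pregnant and potentially pregnant patients are excluded at entry, and that the retention and harms sections could be read to include withdrawn patients. Neither section says so, and the withdrawal rule points the other way.

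**Conclusion.** The point holds in a limited form. The section on discontinuing the intervention makes study withdrawal its only action, and makes it mandatory for pregnancy and for investigator-judged ineligibility, with no exception for patients already implanted. No other section repairs this. The likely cost is outcome data up to 24 months and, for withdrawals before 3 months, adverse-event data and the primary outcome.

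The size cannot be estimated. The illustrations assume that all 10 patients are implanted, that 0 to 3 are withdrawn before 3 months, and that nothing is collected afterwards. The efficacy figures further assume 5 responders and that only non-responders are lost. They show how much a few patients can move the results, not what will happen. This is an inexpensive improvement worth making, and it does not show that the trial's safety data will be deficient.

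**What to change.** Amend the section on discontinuing or modifying the intervention so that it separates two events.

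1. *Discontinuation of the study intervention*, including stops led by pregnancy or by the investigators. Subject to the patient's consent, adverse-event collection and the existing questionnaire visits continue. The reason, where given, and the device status are recorded.
2. *Withdrawal of consent for follow-up.* Only this ends data collection.

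Then reconcile the section with Clinical assessments (removal considered without withdrawal), Secondary outcomes (the 3-month adverse-event window and the visits to 24 months), the retention section (who counts among all patients) and the harms section (whether serious-event collection covers patients no longer on the intervention). If the full protocol already makes this separation, the article's wording should be brought into line with it.

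No rule on stimulation, device removal or imaging is proposed. The cost is a short amendment with matching consent wording. The downside is following a few more patients at visits already in the schedule.
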